### Data collection and outcome measurement

The evaluation will follow a mixed-methods approach with a panel of repeated measures (Fig. 3). Post baseline, follow-up survey 1 (six months after baseline), will examine the panel for seasonality and short-term changes across the different treatment arms. A process evaluation will be undertaken 18 months after baseline to provide data for minor adjustments to the SELEVER design. Follow-up survey 2 will provide evidence on two-year impacts during the lean season, while end line survey 1 will provide evidence on the impact of SELEVER after three years of implementation. End line survey 2 will provide evidence on sustained effects one year after SELEVER completed implementation. The panel design with repeated measures will also allow studying the intervention effects on the growth and nutritional status of children from birth throughout early childhood. The data collection includes child-, caregiver-, household-, and village-level data collection and will be undertaken using electronic tablets (Table 3).

**Fig. 3 Fig3:**
[figure not shown]
Stylized high-level data collection timeline

**Table 3 Tab3:** Measurement schedule for key study indicators

*Main trial comparisons*			Survey round				
Longitudinal, 1800 households			BL (Feb 2017)	R2 (Aug 2017)	R3 (Aug 2019)	R4 (Feb 2020)	R5 (Feb 2021)
Primary	Dietary intake	Dietary diversity (women and children)	I			I	I
	IYCF practices	Minimum acceptable diet (6–24 months)	I			I	I
	Poultry output	Production, sales, and profits	I			I	I
Secondary	Women’s empowerment	WEAI	I			I	I
	Maternal stress and wellbeing		I			I	I
	Poultry VC		I			I	I
	Morbidity	Recall of diarrhea, fever, and chest infections	I			I	I
	Hygiene	Exposure to poultry feces and cleanliness	O			O	O
		Hygiene knowledge	I			I	I
	Women’s nutrition knowledge	Nutrition KAP	I			I	I
	Nutrition	Anthropometry	M			M	M
	Expenditures		I			I	I
	Other household and maternal factors		I			I	I
*WASH sub-study comparisons*			Survey round				
Longitudinal, 1080 households			BL (Feb 2017)	R2 (Aug 2017)	R3 (Aug 2019)	R4 (Feb 2020)	R5 (Feb 2021)
Primary	Dietary intake	Probability of adequacy (Fe, Zn, Vit A), IDDS	I	I	I	I	I
	IYCF practices	Minimum acceptable diet (6–24 months)	I	I	I	I	I
	Poultry output	Production, sales, and profits	I	I	I	I	I
Secondary	Maternal stress and wellbeing		I	I	I	I	I
	Poultry VC		I	I	I	I	I
	Morbidity	Recall of diarrhea, fever, and chest infections	I	I	I	I	I
	Hygiene	Exposure to poultry feces and cleanliness	O	O	O	O	O
		Hygiene knowledge	I	I	I	I	I
	Women’s nutrition knowledge	Nutrition KAP	I	I	I	I	I
	Nutrition	Anthropometry	M	M	M	M	M
	Expenditures		I	I	I	I	I
	Other household and maternal factors		I	I	I	I	I
	Micronutrient status (children)	Hemoglobin (Hb)	B			B	B
		Plasma ferritin (PF)	B			B	B
		Soluble transferrin receptor (sTfR)	B			B	B
		Retinol-binding protein (RBP)	B			B	B
	Infection (children)	Serum C-reactive protein (CRP)	B			B	B
		α-1-acid glycoprotein (AGP)	B			B	B
		Malaria	B			B	B
		Pathogenic gut bacteria	S			S	S
	Cognition (children)		T			T	T

*B* blood, *BL* baseline, *I* interview, *IDDS* individual dietary diversity score, *IYCF* infant and young child feeding, *KAP* knowledge attitude practices, *M* measurement, *O* observation, *R* follow-up round, *S* stool, *T* test, *WEAI* Women’s Empowerment in Agriculture Index

#### Dietary assessment and anthropometry measurements

Within each survey household, basic anthropometric data collection will include all women of childbearing age (aged 15–35 years), all children aged < 5 years at baseline, and all children born within the households during the years between the baseline and end line surveys. A sub-sample of index women and children dyads (pairs) will be randomly selected for in-depth assessment, including a dietary assessment and biomedical tests. Dietary assessment will be undertaken by trained and supervised enumerators using the interactive 24-h recall multiple-pass method at each survey round [21]. The recall will be repeated at each round on a non-consecutive day on 15–20% of the sub-sample for the calculation of usual nutrient intakes. Prior to the recall interview, caregivers will be briefed on the purpose and methods of interview. The interview will be conducted using visual aids to assist in estimating portion sizes of the foods consumed. A short food frequency questionnaire assessing the frequency of consumption of more nutrient dense foods like poultry and other meat products over the last month will be included in the 24-h recalls. The child’s weight will be recorded using an electronic scale (SECA 876, Germany) to the nearest 100 g. Height or length will be measured to the nearest 0.1 cm using portable fixed base stadiometers or length boards (SECA 417, Germany). Mid-upper arm circumference (MUAC) will be recorded by using non-stretchable tape with 0.1 cm precision (SECA 201, Germany). All measurements will be taken in duplicate by an anthropometrist and an assistant. All measurements will be exercised before the study through standardization exercises. From these standardization sessions, inter-observer and intra-observer variation of measurement error will be documented. Maternal MUAC, weight, and height will also be recorded using non-stretchable tape (SECA 201), scales (SECA 877), and stadiometers (SECA 217, Germany), respectively. WHZ and HAZ scores will be calculated using the 2006 WHO growth standards [22]. IYCF knowledge and practices of caregivers will be assessed using a structured questionnaire based on the WHO guidelines [22].

#### Assessments of micronutrient and infection status

Blood and stool samples will be collected at baseline and year 3 and 4 end lines as part of the WASH sub-study. Infection biomarkers in the women and children dyads include serum C-reactive protein (CRP) and α-1-acid glycoprotein (AGP). Additional indicators on the presence of specific bacterial gut infections in stools will also be included in children. The potential list of pathogenic bacteria includes *Salmonella* spp., *E. coli*, enteropathogenic *E. coli* (EPEC), enterohemorrhagic *E. coli* (EHEC), *E. coli* genotypes associated with resistance to β-lactam antibiotics (extended spectrum beta-lactamase [ESBL]), *Staphyococcus aureus*, *Giardia intestinalis*, *Campylobacter jejuni*, methicillin-resistant *S. aureus* (MRSA). EED biomarkers in stools will include alpha-1-antitrypsin (AAT), neopterin (NEO), and myeloperoxidase (MPO). A heel or finger prick blood drop will be used to measure hemoglobin concentrations (using a Hemocue haemoglobinometer) and *Plasmodium* infection (using rapid diagnostic tests). An additional 300 μL of blood will be collected in lithium-heparin-coated microvettes (CB 300; Sarstedt) for measurement of retinol-binding protein (RBP), plasma ferritin (PF), transferrin receptor (TfR), CRP, and AGP concentrations. Immediately after phlebotomy, pre-labeled microvettes will be placed in an ice chest/cold box with ice packs, maintained at 0–8 °C for transportation to a central laboratory. Transport of the blood samples from the field will be on a daily basis and the samples will be processed no later than 24 h after phlebotomy. Precautions will be taken to maintain proper temperature and to avoid physical shocks in order to prevent hemolysis of blood cells during transportation. Upon arrival at the central laboratory, the blood samples will be centrifuged for plasma separation. For analysis, 100 uL of plasma will be aliquoted. The remaining plasma will be stored separately as a back-up. Pre-printed labels having identical numbers will be provided to the technicians at the central laboratory for use on the aliquots containing plasma before placing them in the freezer. The samples will be temporarily stored in a freezer at – 22 °C in the central laboratory. The aliquots will be shipped on dry ice to VitA-Fe Tech laboratories (Willstaett, Germany) for the micronutrient and inflammation marker analyses by enzyme-linked immunoassay [23].

#### Women’s empowerment and wellbeing

Women’s empowerment will be measured over the five domains of the Women’s Empowerment in Agriculture Index (WEAI), which include decisions about agricultural production, access to and decision-making power over productive resources, access to financial resources, leadership in the community, and time use. For this study, we will be using the project-level WEAI (pro-WEAI) and will also include modules on self-efficacy and decision-making with respect to health and nutrition. Maternal stress and wellbeing will be measured subjectively using validated scales such as Perceived Stress Scale (PSS). The interviews will also examine men’s knowledge and attitudes regarding the nutrition of women and children around the first 1000 days, women’s time and status and their productive and reproductive roles, fathers’ role in ensuring adequate health and nutrition of their family, and domestic violence.

#### Poultry value chain

Poultry VC-related data collected will include knowledge of improved poultry-production practices, input use and access to credit, poultry production and mortality, poultry marketing and transaction costs, and investments (e.g. housing).

#### Morbidity, hygiene, health and nutrition knowledge, and practices

Morbidity will be assessed through symptoms of acute respiratory infections, diarrhea, and fever in study children recalled through caregiver interviews over the last week and the last three days. Exposure to poultry feces and cleanliness of mother and child, kitchen, house, and compound will be measured by spot-check observations. Hygiene knowledge will be assessed using a questionnaire previously tested in Burkina Faso and practices will be measured by 24-h recall methods. The survey will include an assessment of women’s knowledge, attitudes, and practices regarding IYCF and sanitation and hygiene, using a questionnaire and 24-h recall methods previously tested in Burkina Faso [24].

#### Other household level data

The household survey will include a range of modules including demographics, consumption/expenditure, and income (gender-disaggregated; total income and income from sale of agricultural production); the consumption/expenditure module will also be used to derive household-level estimates of energy and micronutrient availability at the household level (and adequacy) using adult equivalents.

### Methods of analysis

#### Impact evaluation

The analysis will follow the intention-to-treat approach as protocol and as treated, using econometric analysis to control for differences at baseline across treatment arms for all the relevant variables of interest. The randomized study design allows for the identification of causal effects of interventions through comparisons of mean outcomes between the treatment arms. Following Bruhn and McKenzie [25], impact will be assessed for the different treatment arms using both a “difference-in-difference” (DID) estimator and a single difference analysis of covariance (ANCOVA) model. In particular, the ANCOVA estimator has been shown to provide more efficient estimates of program impact when auto-correlation of outcomes is low [25]. Depending on the level of clustering of the outcome under analysis, we will employ multi-level regression models that account for the hierarchical nature of the data [26]. The multi-level models, also known as mixed-effects models, will use both fixed effects (as covariates) and random effects at commune, village, and household levels to take into account the effect of clustering at these levels and to estimate unbiased standard errors. Robustness checks for the treatment estimates will also include controlling for the balancing variables used in the randomization. The intent-to-treat analysis strategy we will employ will include attempts to follow up all individuals in the randomized study, as well as the development of a main analysis that is valid under a stated plausible assumption on missing data, and sensitivity analysis to explore the effects of departures from the assumption underlying the main analysis. Data management, data cleaning, and statistical analyses will be conducted using Stata (Statacorp, USA). The statistical significance for all tests will be set at 5% in case of testing main effects or 10% in case of interactions. All statistical tests will be two-sided.

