### Random assignment and manipulation of treatments

Communities will be randomly assigned to one of three treatment arms:SELEVER intervention group: communities where the SELEVER program is implemented;SELEVER+: communities where the SELEVER program is implemented alongside an intensive WASH component;Control group: communities with no intervention, for at least the four years of the study duration.

The SELEVER intervention is implemented at the commune level as the training, sensitization, and BCC involve commune level stakeholders. During the preparation stage, 60 communes were selected from a pool of 79 communes that were available for scale-up by SELEVER in the targeted regions. The criteria for commune selection included: (1) not included in the SELEVER pilot communes; (2) classified as rural or peri-urban (as classified in the national census); (3) year-round accessibility by road; and (4) for the Hauts-Bassin region communes, proximity to the Boucle de Mouhoun and Centre Ouest regions. The first stage of randomization was aimed at randomizing the 60 communes in the study into two groups (SELEVER and control) and provides the basis for the main trial comparisons (SELEVER – Control). Due to the relatively small number of clusters in the study, to ensure balance in the comparison groups the random allocation was undertaken through restricted randomization by modeling selection using a set of commune-level and village-level variables obtained through the national census of 2006.

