### Sample sizes

Power calculations (Table 2) and resource availability suggested the adoption of a dual sampling strategy: For the outcomes in the main trial comparison (SELEVER vs. control), 15 households from each of the 120 villages in the study will be surveyed at baseline and end line surveys, for a total of 1800 households. A sub-sample of 1080 households, women and children dyads (or pairs) will be included for detailed and more frequent assessments (see “Data collection and outcome measurement”).

**Table 2 Tab2:** Minimum detectable effect size estimates and summary of parameters used in sample size calculations for the main study outcomes^a^

	Women’s dietary MPA	Children’s dietary MPA (3–5 years)	Children DD (6–24 months) (n. of food groups)	Household poultry production	Household poultry sales
Communes (n per intervention arm)	15	15	30	30	30
Villages (n per intervention arm)	30	30	60	60	60
Individuals per village (n)	12	12	8.8	15	15
Intra-cluster correlation (level 3)	0.002	0.002	0.001	0.001	0.001
Intra-cluster correlation (level 2)	0.05	0.04	0.05	0.06	0.01
Sample size (per intervention arm)	360	360	526	900	900
Estimated baseline levels	0.26	0.43	3.95	11	1
Standard deviation (baseline)	0.22	0.31	0.97	11	3
Minimum detectable effect size (SD)	0.28	0.27	0.21	0.18	0.15
Minimum detectable effect size (eq. levels)	0.06	0.08	0.20	1.98	0.45

^a^Estimates based on type I error of 5% (two-sided test) and statistical power of 80%

*MPA* mean probability of adequacy, *DD* dietary diversity

During the baseline survey, a household census will be conducted to identify all the large poultry producers in the community, households with women in the target groups (women aged 15–35 years with children in the target age group), and collect other basic household level information necessary for the sample selection. Households will then be randomly selected from the household census for the survey interviews. Large poultry-producing households (e.g. defined as owning a poultry flock of over 20 chickens/fowls) will be oversampled (6/15 households will be large poultry-producing households). This distribution of the sample will enable the construction of comparable samples for the main trial comparisons, also allowing for analysis of direct and indirect effects by including both beneficiary and non-beneficiary households in the survey population.

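### With random intercepts only, the difference-in-difference model leaves clustering of change between rounds out of its standard error, so the claim of unbiased standard errors is not assured for that estimator

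*Protocol article*

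**What the plan says.** Under Impact evaluation, the protocol article will estimate effects "using both a “difference-in-difference” (DID) estimator and a single difference analysis of covariance (ANCOVA) model". It does not rank one above the other, though it notes that ANCOVA is more efficient when outcomes are weakly autocorrelated. On clustering it says: "Depending on the level of clustering of the outcome under analysis, we will employ multi-level regression models". These models are to include covariates as fixed effects, together with "random effects at commune, village, and household levels to take into account the effect of clustering at these levels and to estimate unbiased standard errors". No DID equation is written out, and no cluster-by-round term or random time slope is named.

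Under Data collection and outcome measurement, the design is described thus: "The evaluation will follow a mixed-methods approach with a panel of repeated measures". Table 3 follows the same households from February 2017 to February 2020 and February 2021. Under Random assignment and manipulation of treatments, the first stage allocates 60 communes to two groups. Table 2 shows two villages per commune, with 30 communes per arm in the main trial and 15 per arm for the MPA outcomes.

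**The concern.** A DID estimate compares the change over time in one arm with the change in the other. In a panel, whatever is constant over time in a commune, village or household is subtracted out before the comparison is made. Random intercepts at those three levels describe exactly these constant parts. They therefore add nothing to the variance of the DID contrast, which is judged against within-household residual variation as if each household changed independently of its neighbours.

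That is correct only if no commune or village moves differently from the others between rounds. The article gives reasons to doubt it. Its Market analysis section allows that poultry markets may not be integrated and that price effects would appear at local markets serving a village or group of villages. The programme targets poultry disease through village-level vaccinators. Baseline and the first end line are three years apart. If change is clustered, DID confidence intervals are too narrow and the false-positive rate exceeds 5%, on primary outcomes as well.

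**Working it through.** **Inputs from Table 2** (J communes per arm, K villages per commune, n individuals per village, commune ICC ρ3, village ICC ρ2):
- Women's MPA: J = 15, K = 2, n = 12, ρ3 = 0.002, ρ2 = 0.05
- Poultry production: J = 30, K = 2, n = 15, ρ3 = 0.001, ρ2 = 0.06
- Poultry sales: J = 30, K = 2, n = 15, ρ3 = 0.001, ρ2 = 0.01

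**Assumed, because the document gives neither:** cluster autocorrelation r (the share of commune and village variance that is stable between rounds) and household autocorrelation h.

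**Step 1. The plan's own figures.** The minimum detectable effect for a single-round comparison is M × √{(2/J)[ρ3 + ρ2/K + (1 − ρ2 − ρ3)/(Kn)]}. With M from the t distribution on 2J − 2 degrees of freedom and 5% attrition, this gives 0.278 for women's MPA, 0.268 for children's MPA, 0.212 for child dietary diversity, 0.186 for production and 0.148 for sales. Table 2 states 0.28, 0.27, 0.21, 0.18 and 0.15. Four agree to rounding. Production agrees without attrition (0.184) or with normal quantiles (0.181). Table 2 thus fits a single-difference comparison that counts the village ICC as noise.

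**Step 2. Variance of the DID contrast, two rounds, balanced panel, total variance 1.** The components that vary between rounds are:
- household: s_e = (1 − h)(1 − ρ2 − ρ3)
- village by round: s_v = (1 − r)ρ2
- commune by round: s_c = (1 − r)ρ3

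The random-intercept model puts all three into one residual: V_model = 4(s_e + s_v + s_c)/(JKn).

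The true variance is V_true = 4[s_c/J + s_v/(JK) + s_e/(JKn)].

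Type I error = 2{1 − Φ(1.96 × √(V_model/V_true))}.

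**Step 3. Worked case, women's MPA, r = 0.5, h = 0.5.** s_e = 0.5 × 0.948 = 0.474, s_v = 0.025, s_c = 0.001.
- Model SE = √(4 × 0.500/360) = 0.0745
- True SE = √{4 × (0.001/15 + 0.025/30 + 0.474/360)} = √(4 × 0.002217) = 0.0942
- SE ratio = 0.79, so type I error = 12.1%

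**Step 4. Type I error over the range.**

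| Outcome | h | r = 1 | r = 0.8 | r = 0.5 |
|---|---|---|---|---|
| Women's MPA | 0.2 | 5.0% | 6.8% | 9.5% |
| Women's MPA | 0.5 | 5.0% | 7.9% | 12.1% |
| Poultry production | 0.2 | 5.0% | 7.7% | 11.6% |
| Poultry production | 0.5 | 5.0% | 9.3% | 15.2% |
| Poultry sales | 0.2 | 5.0% | 5.5% | 6.2% |
| Poultry sales | 0.5 | 5.0% | 5.8% | 7.0% |

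At r = 0.9 and h = 0.5 the three outcomes give 6.5%, 7.2% and 5.4%.

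**Step 5. Simulation (h = 0.5; r = 1, 0.8, 0.5).** With standard errors that ignore clustering of change, the error rate was 5.1%, 7.6% and 12.0% for women's MPA (4,000 runs) and 4.7%, 9.1% and 14.9% for production (3,000 runs). A test on commune-level mean change stayed between 4.7% and 5.3% throughout.

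**Step 6. Do the intercepts really cancel?** A mixed model with commune, village and household intercepts was fitted to two simulated data sets. In each, the treatment-by-time estimate was identical to that from an unclustered analysis of change. The standard errors were 0.0695 against 0.0695, and 0.0765 against 0.0762.

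**The case against.** The strongest objection is that the article names levels of clustering, not a full specification. It does not say intercepts only. A random time slope or a cluster-by-round effect is also a random effect at commune or village level, and an analysis plan that is not shown may include one. This stands against any claim that the plan rules such terms out. It does not dispose of the point, because the article goes beyond silence: it lists the effects and says what they achieve, and on the usual reading they do not achieve it for DID.

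Second, ANCOVA is planned alongside DID. With one follow-up record per person, commune and village intercepts do carry the clustering, so each outcome measured at baseline and follow-up in the same person or household has an estimate that this problem does not touch. That stands. But since DID is not ranked below ANCOVA, a DID result could still carry a conclusion.

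Three stronger readings are tempting and not supported:
- A reader might infer that every DID result exceeds 5%. It does not if cluster effects are stable (r = 1), and the excess is small for poultry sales.
- A reader might infer that the clustered model is used only if clustering is observed. The wording on the level of clustering most naturally means the hierarchical level at which the outcome sits, since the next sentence lists those levels.
- A reader might quote larger error rates by assuming a commune ICC well above Table 2's 0.001 to 0.002. Nothing in the document supports such a value.

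**Conclusion.** The concern holds in conditional form. If the listed random effects are intercepts, the DID standard error omits commune- and village-specific change, and the statement about unbiased standard errors is not assured for that estimator. Under r = 0.8 to 0.5 and h = 0.2 to 0.5, the true standard error is 1.08 to 1.26 times the reported one for women's MPA, 1.11 to 1.37 times for poultry production and 1.02 to 1.08 times for poultry sales. The corresponding type I errors are about 7-12%, 8-15% and 5.5-7%. Both autocorrelations are assumptions, so the direction is firm whenever r is below 1, but the size cannot be fixed from the document. The figures also assume two rounds and a balanced panel. Single-follow-up ANCOVA is not affected.

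**What to change.** State that DID and any other model using more than one round will include commune-by-round and village-by-round random effects, or will use standard errors clustered by commune. Either way, apply a small-sample correction: about 28 degrees of freedom for 15 against 15 communes (2 × 15 − 2) and 58 for 30 against 30 (2 × 30 − 2). Limit the statement about unbiased standard errors to models that contain these terms.

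The cost is a sentence in the analysis section and a few lines of Stata code. No data collection changes. DID intervals will widen, by roughly the ratios given above if the assumed autocorrelations are right, and hardly at all if cluster effects prove stable.
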